## Abstract

**Introduction::**

Infective endocarditis (IE) and other severe infections induce significant changes in the immune response in a considerable number of affected patients. Numerous IE patients develop a persistent functional immunological phenotype that can best be characterized by a profound anti-inflammation and/ or functional “anergy.” This is pronounced in patients with unresolved infectious foci and was previously referred to as “injury-associated immunosuppression” (IAI). IAI can be assessed by measurement of the monocytic human leukocyte antigen-DR (mHLA-DR) expression, a global functional marker of immune competence. Persistence of IAI is associated with prolonged intensive care unit length of stay, increased secondary infection rates, and death. Immunomodulation to reverse IAI was shown beneficial in early immunostimulatory (randomized controlled) clinical trials.

**Methods::**

Prospective 1:1 randomized controlled clinical study to compare the course of mHLA-DR in patients scheduled for cardiac surgery for IE. Patients will receive either best standard of care plus cytokine adsorption during surgery while on cardiopulmonary bypass (protocol A) versus best standard of care alone, that is, surgery without cytokine adsorption (protocol B). A total of 54 patients will be recruited and randomized. The primary endpoint is a change in quantitative expression of mHLA-DR (antibodies per cell on CD14+ monocytes/ macrophages, assessed using a quantitative standardized assay) from baseline (preoperation [pre-OP], visit 1) to day 1 post-OP (visit 4).

**Discussion::**

This randomized controlled clinical trial (RECReATE) will compare 2 clinical treatment protocols and will investigate whether cytokine adsorption restores monocytic immune competence (reflected by increased mHLA-DR expression) in patients with IE undergoing cardiac surgery.

**Trial registration::**

This protocol was registered in ClinicalTrials.gov, under number NCT03892174, first listed on March 27, 2019.

## Introduction

1

Infective endocarditis (IE) is a life-threatening clinical condition that is characterized by infection of the endo-(myo)cardium and cardiac valves.^[1]^ IE treatment depends on the severity of the infection and induced tissue damage. As first-line clinical therapy, systemic intravenous antibiotic treatment according to international guidelines is applied.^1^,^2^ In severe IE affecting the function of heart valves, surgical repair and replacement can be deemed necessary. The decision when to operate on a patient is based on internationally approved guidelines^[2]^ and depends on expected or observed complications, severity of valve dysfunction, and size of vegetation(s).^[1]^ The aim of surgery is to control the site of infection and to restore (normal) heart function while repairing or replacing the infected valve and to repair associated defects (abscess). During cardiac surgery itself, the use of a cardiopulmonary bypass circuit is required.

Severe infections, such as IE, are known to induce significant changes in a hosts’ immune response.^3^,^4^,^5^,^6^,^7^ In fact, numerous patients with IE develop a persistent functional immunological phenotype that can best be characterized by a profound anti-inflammation and functional immunological anergy.^3^,^5^,^8^ This seems especially the case in patients with unresolved infectious foci and was previously referred to as “injury-associated immunosuppression” (IAI).^[3]^ IAI can be assessed by measurement of the monocytic human leukocyte antigen-DR (mHLA-DR) expression, a standardized “global” biomarker of immune competence.^8^,^9^ Persistence of IAI is associated with prolonged intensive care unit (ICU) length of stay, increased secondary infection rates, and death.^[3]^

Immunomodulatory therapies aiming to reverse IAI and were shown beneficial in early clinical trials.^10^,^11^ Recent expert panels suggest evaluation of clinical immunomodulatory strategies, including extracorporeal approaches.^[4]^ We could previously show that assessment of the surface expression of HLA-DR on monocytes/macrophages correlates with the functional status of the cellular immune system in critical illness and may be regarded as a global marker of cellular immune function in ICU patients.^3^,^10^,^11^ An intervention to reduce immune mediators may affect the net dysregulated immunological response,^[11]^ that is, to restore functional immunocompetency. Via comparison of 2 clinical protocols (i.e., cardiopulmonary bypass with cytokine adsorption plus best standard of care vs best standard of care alone), we will investigate whether adsorption modulates functional cellular immunocompetence,^[9]^ which was shown of prognostic importance in the postoperative course of respective patients.^[3]^ Cytokine adsorption will be performed during cardiopulmonary bypass with a European Conformity (CE)-marked medical device approved for this indication. Studies have confirmed the safety of this device, but no data on direct immunological effects (i.e., change in net immune status) are available.^11^,^12^,^13^,^14^,^15^,^16^,^17^

We therefore embarked to investigate in a 1:1 randomized controlled clinical trial whether intraoperative cytokine adsorption would improve mHLA-DR expression and thus immune competence.

## Methods

2

### Type of study

2.1

Cytokine REmoval in CRitically ill pAtients requiring surgical Therapy for infective Endocarditis (RECReATE) is an investigator-initiated, prospective, single-center randomized controlled clinical trial. Sponsor is [name] from the Department of Cardiovascular Surgery of Inselspital, Bern University Hospital. Cytokine adsorption will be performed using a CytoSorb adsorption device (Cytosorb GmbH, Berlin, Germany), a CE-marked and approved medical device for treatment of patients with IE undergoing cardiac surgery. Cytokine adsorption will be employed during surgery for IE on cardiopulmonary bypass only. The study is performed in a tertiary care academic center (University of Bern, Inselspital, Bern, Switzerland) at the Departments of Intensive Care Medicine, Cardiovascular Surgery, and the Department of Anaesthesiology and Pain Medicine. Recruitment started in November 2019 (ongoing) and the actual protocol version is V1.2, dated August 8, 2019.

### Approvals/trial registration

2.2

This study was approved by the respective competent local ethics committee on human research (Kantonale Ethikkomission, Bern, Switzerland, approval number 201901038). Informed consent will be achieved from all participants/legal representatives. This protocol was registered on March 27, 2019 at clinicaltrials.gov (NCT03892174) before study start. The study is carried out in accordance with the protocol and principles enunciated in the current version of the Declaration of Helsinki, the guidelines of Good Clinical Practice issued by International Council for Harmonization of Technical Requirements for Pharmaceuticals for Human Use (ICH). Results will be published in a peer-reviewed journal and disseminated at international conferences.

### Study design

2.3

This study is a prospective 1:1 randomized single-blinded (subject blinded) controlled clinical trial including IE patients scheduled for surgery. All patients scheduled for cardiac surgery due to IE are screened for potential study inclusion. Patients willing to participate after having been fully informed about the study by a cardiac surgeon will have to sign written informed consent. Any patient who discontinues the study will be replaced. Study procedures are performed according to the planned time schedule in adherence to visit intervals indicated given in the SPIRIT diagram (Table 1).

**Table 1 T1:**
[figure not shown]
SPIRIT figure indicating visits/study-specific assessments.

### Population and sample size calculation

2.4

Fifty-four patients undergoing planned surgical treatment for IE will be randomly allocated (1:1 allocation) to receive either best standard of care plus cytokine adsorption (protocol A) or best standard of care alone (protocol B). Allocation to the groups, protocol A or protocol B, is done computerized using the REDCap software. The null hypothesis is that there is no differences in mHLA-DR expression (readout: monoclonal antibodies [mAb/cell]) between the 2 groups. Assuming the response to be normally distributed within each subject group with a standard deviation of 3200 mAb/cell and a true difference in the arms means of 2500 mAb/cell (10,000 vs 7500 mAb/cell of mHLA-DR expression), n = 27 patients will be required to be able to reject the null hypothesis that the population means of the experimental and control groups are equal with probability (power) of 0.8. The type I error probability associated with this test of this null hypothesis is 0.05 (2 sided).

The following inclusion criteria apply:

1.Subjects scheduled for cardiac surgery for infectious endocarditis (according to DUKE criteria) with antibiotic therapy for ≤14 days.2.Presence of informed consent3.Age ≥18 years.

The following exclusion criteria apply:

1.Known previous treatment (last 6 months) with immunologically active biologicals or specific immunomodulatory drugs (e.g., rituximab).2.Known high-dose chronic (i.e., before onset of infectious endocarditis) steroid medication with prednisone equivalent of >30 mg/day.3.Patients on extracorporeal membrane oxygenation (ECMO), or any other (preoperative) cardiac assist device.4.Moribund patient (life expectancy <14 days, as judged by investigator).

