#### Primary endpoint

2.5.2

1.Change in quantitative expression of mHLA-DR (given in antibodies per cell [Ab/cell] on CD14+ monocytes/ macrophages, assessed using a standardized quantitative assay) from baseline (preoperation [pre-OP], visit 1) to day 1 post-OP (visit 4).

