### Analysis of results

2.8

The primary analysis will be performed on the full data set, that is, the intention-to-treat population. In an additional per-protocol analysis, we will exclude patients with major protocol deviations or missing primary outcome data.

We will apply a linear model corrected for the baseline value to analyze the mean change in quantitative expression of mHLA-DR (mAb/cell on CD14+ monocytes/macrophages) in patients treated with protocol A versus protocol B, namely the following quantity: 

, with 

 being the protocol A quantitative expression of mHLA-DR at times 1 and 3 respectively and 

 being the protocol B quantitative expression of mHLA-DR at times 1 and 3, respectively, and 

 being paired averages. We will assess the normality of model residuals and if the approximate normality is not satisfied we will use transformations of *Y*
_*ij*_ and *X*
_*ij*_ (with log or Box-Cox transformations). In case we do not achieve normality with any transformation we will use the Wilcoxon-Mann-Whitney test for comparing distributions of 

 and 

.

We will assess the AUC for the quantitative expression of mHLA-DR over time by computing the surfaces under the trajectories of quantitative expression of mHLA-DR and abscissa axis per subject, compute the averages per protocol group, and compare these averages either with an unpaired *t* test (eventually with transformations for normality) or a nonparametric Wilcoxon-Mann-Whitney test.

We will compare the average protocol trajectories of the quantitative expression of mHLA-DR, inflammatory markers, and organ dysfunction by fitting the following mixed-effects model: 

 (baseline value is added as a covariate) with *i* being the subject; *j* the protocol; *t* the time-point 2, 3, or 4; *G*
_*ij*_ the protocol corresponding to subject *i*; *X*
_*ij*_ is the quantitative expression of mHLA-DR at time 1; *T*
_*it*_ the time-point 2, 3, or 4 for subject *i*, *ε*
_*ijt*_ residuals, and *α*
_*i*_ random effect capturing the individual variability of subject *i*. Testing the hypothesis *γ*
_4_ = 0 is equivalent to testing the protocol effect over time under assumption of good model fit.

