## Discussion

3

Previous data show that functional impairment of cell-mediated immunity reflects an additional “organ” dysfunction in the context of life-threatening injury, such as severe infection.^3^,^5^,^17^ Although large-scale clinical data are missing, IE is known to trigger several humoral and immune cellular pathways, often resulting in a state of immunosuppression in affected individuals, and this was shown of prognostic importance in critically ill patients.^3^,^18^

In the current investigator-driven clinical study RECReATE, we aim to analyze the impact of a cytokine removal strategy (1 treatment session during cardiopulmonary bypass) on key humoral and cellular immune response mechanisms. In brief, we strive to explore whether cytokine adsorption can increase (or even restore) monocytic immune competence (assessed by mHLA-DR expression) in surgically treated patients with IE. Data from previous clinical studies investigating immunostimulatory^[10]^ and selective extracorporeal cytokine removal strategies^[11]^ demonstrate that monocytic function (mHLA-DR-expression) can be restored using comparable measures. Thus, it seems likely that treatment using this alternative cytokine removal strategy will result in increased mHLA-DR expression, reflecting improved monocytic immune function.

Our study has a number of limitations that deserve discussion. First, this is a single-center pilot study with inherent limitations (including limited external validity) set by the chosen study design. Findings in this pilot study should therefore be confirmed in subsequent multicentre investigations. Importantly, however, the primary endpoint is assessed using a standardized quantitative assay with an adequate inter- (and intra-) coefficient of variation shown in multinational comparison studies.^[8]^ Second, although the sample size appears rather limited in this pilot study, it might be considered a strength of the current analysis that the sample size calculation/ power regarding the primary endpoint was partly based on data from respective previous clinical studies. Third, optimal “dose” of the cytokine adsorption applied is currently unknown and, theoretically, one might speculate that the applied “adsorption dose” (treatment only while patients are on cardiopulmonary bypass) might be insufficient. However, this best reflects current practice, in which physicians might chose to prescribe cytokine adsorption based on personal preference.

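### Sizing on mHLA-DR levels is conservative for the baseline-adjusted primary model, but the last-resort Wilcoxon test drops the baseline and could lose power

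*Protocol article*

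**What the plan says.** Section 2.4 states the null hypothesis as "there is no differences in mHLA-DR expression" between the groups. It assumes a response "normally distributed within each subject group with a standard deviation of 3200 mAb/cell" and "a true difference in the arms means of 2500 mAb/cell", illustrated as "10,000 vs 7500 mAb/cell of mHLA-DR expression". With a two-sided 5% test it arrives at 27 patients, which is per arm given the total of 54, "with probability (power) of 0.8". No test is named, and neither change nor a baseline to day-1 correlation is mentioned.

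Section 2.5.2 defines the primary endpoint as the change in mHLA-DR "from baseline (preoperation [pre-OP], visit 1) to day 1 post-OP (visit 4".

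Section 2.8 sets out the primary analysis in three steps: a linear model of mean change, corrected for the baseline value; log or Box-Cox transformation if the residuals are not close to normal; and then the last resort: "In case we do not achieve normality with any transformation we will use the Wilcoxon-Mann-Whitney test for comparing distributions of" two quantities whose symbols did not survive text extraction.

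The Discussion offers as a possible strength that "the sample size calculation/ power regarding the primary endpoint" rested partly on data from earlier studies.

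**The concern.** The power calculation concerns one quantity (the level) and the endpoint another (the change). Under randomisation the expected baselines are equal, so a 2500 difference in day-1 level is also a 2500 difference in mean change. Only the SD is at issue.

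That SD depends on the analysis. A model adjusted for baseline has a residual SD no larger than the SD of the level. An unadjusted change score can have a larger SD if baseline and day 1 are weakly correlated. A two-group Wilcoxon-Mann-Whitney test has no place for a covariate, so moving to it discards a baseline measurement that the trial collects anyway. A null result reached by that route would be read against a power of 0.8 that was never worked out for it.

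**Working it through.** **Inputs.** From section 2.4: difference 2500, SD 3200, 27 per arm, two-sided alpha 0.05. Assumed, because the article does not give them: SD 3200 is the SD of the level at both visits, and the baseline to day-1 correlation r takes values from 0 to 0.7.

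**Step 1: the plan's own figure.** Two-sample t test on levels:
- standard error = 3200 × √(2/27) = 871
- noncentrality = 2500/871 = 2.87, on 52 df
- power = 0.804; with 26 per arm it is 0.789

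So 27 per arm is exactly the answer for a t test on levels.

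**Step 2: the planned primary model.** Adjusting change for baseline gives the same treatment effect as adjusting the day-1 level for baseline. The residual SD is 3200 × √(1 − r²), with 51 df.

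**Step 3: unadjusted change.** The SD is 3200 × √(2(1 − r)), with 52 df for the t test. For Wilcoxon, the per-arm n is multiplied by the asymptotic relative efficiency under normality, 0.955.

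| r | Adjusted SD | Power, adjusted model | Change SD | Power, t test on change | Power, Wilcoxon on change |
|---|---|---|---|---|---|
| 0 | 3200 | 0.80 | 4525 | 0.51 | 0.49 |
| 0.3 | 3053 | 0.84 | 3786 | 0.66 | 0.64 |
| 0.5 | 2771 | 0.90 | 3200 | 0.80 | 0.79 |
| 0.7 | 2285 | 0.98 | 2479 | 0.95 | 0.94 |

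Simulation with normal data gave 0.48, 0.64, 0.78 and 0.94 for the last column.

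**Step 4: non-normal data.** The fallback applies only when normality fails, so the normal-data figures are indicative. Simulated power of Wilcoxon on change with bivariate t data of the same SD:

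| Tails | r = 0.3 | r = 0.5 |
|---|---|---|
| 5 df | 0.73 | 0.87 |
| 4 df | 0.78 | 0.90 |
| 3 df | 0.88 | 0.96 |

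**Step 5: a fallback that keeps the baseline.** Simulated power of rank analysis of covariance (day-1 value on baseline) against Wilcoxon on change:
- normal, r = 0.3: 0.82 against 0.64
- normal, r = 0.5: 0.87 against 0.78
- t with 5 df, r = 0.3: 0.89 against 0.73

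Type I error stayed near 0.05. At r = 0 with normal data the baseline carries no information, and the rank analysis behaves like a Wilcoxon test on day-1 levels, with power about 0.78 to 0.79.

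**Step 6: the other reading of the SD.** If 3200 is already the SD of change, Wilcoxon on change has power about 0.78 to 0.79. The adjusted residual SD becomes 3200 × √((1 + r)/2), that is 2580, 2771 and 2950 for r = 0.3, 0.5 and 0.7, with power 0.94, 0.90 and 0.86.

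**The case against.** The strongest reply is that nothing in the calculation is wrong. The figure reproduces, and sizing a baseline-adjusted analysis with an unadjusted t test is an ordinary conservative choice. That stands, and it disposes of the primary model.

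Three further objections limit what is left:
- The fallback is remote. It is reached only after log and Box-Cox transformations have failed, and right skew, the usual departure for a cytometry count, is what those transformations handle. This stands, but the plan still names the test for its primary endpoint.
- The quantities compared by the fallback are missing from the extracted text, so that it compares changes is an inference. It is a reasonable one, because the endpoint is change and the surrounding text uses values at two times. If the test compared day-1 levels instead, it would still take no baseline and would not be a test of the stated endpoint.
- The correlation and the source of the SD are details that an article may leave to the full protocol. Their absence is therefore not the point here. The point is the choice of fallback test, which the article does make.

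A reader might infer that the trial is underpowered, or that the fallback misses 0.8 whenever the correlation is below 0.5. The documents support neither. The first fails on step 2. The second fails on step 4, where heavy-tailed data give 0.88 at a correlation of 0.3.

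**Conclusion.** The stated power of 0.8 is sound and conservative for the planned baseline-adjusted model: 0.80 to 0.98 for assumed correlations of 0 to 0.7, with 27 per arm. No change in sample size is called for.

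The point that holds is narrower. The prespecified last-resort test gives up the baseline adjustment and with it the assurance of about 0.8. Under normality its power could be as low as about 0.48 at zero correlation and 0.64 at 0.3. It is about 0.78 at 0.5 and 0.94 at 0.7. Heavier tails raise it. A shortfall is thus possible at low correlation, but not shown.

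This rests on three assumptions: that the fallback compares unadjusted changes, that 3200 is the SD of the level at both visits, and that the correlation lies in the range shown. If 3200 is the SD of change, the shortfall almost vanishes. The point is a modest improvement to a contingency analysis and does not affect the main design.

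**What to change.** In section 2.8, or in the analysis plan, replace the Wilcoxon-Mann-Whitney fallback for the primary endpoint with a nonparametric analysis that keeps the baseline. Rank analysis of covariance of the day-1 value on baseline is the option whose power is shown above: it was about 0.8 or more in the scenarios checked and at least as good as Wilcoxon on change. A permutation test of the baseline-adjusted effect would serve the same purpose, though its power was not computed here.

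In section 2.4, add two clarifications: that 0.8 comes from a t test on day-1 levels and is conservative for the baseline-adjusted model, and whether 3200 is the SD of the level or of the change.

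The cost is a few sentences. No patients, visits or measurements are added. The only drawback is a test that is slightly less familiar to readers.

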### Outcome measures

2.5

#### Objectives

2.5.1

The purpose of this study is to compare 2 clinical protocols and to investigate whether cytokine adsorption during surgery can modulate the function of monocyte/macrophages, which are key immune cells in patients with severe infections. Monocytic immune competence is assessed by standardized quantitative flow cytometric measurement of mHLA-DR (BD Quantibrite-HLA-DR/Monocyte-BD Biosciences).

#### Primary endpoint

2.5.2

1.Change in quantitative expression of mHLA-DR (given in antibodies per cell [Ab/cell] on CD14+ monocytes/ macrophages, assessed using a standardized quantitative assay) from baseline (preoperation [pre-OP], visit 1) to day 1 post-OP (visit 4).

#### Secondary endpoints

2.5.3

1.Change in mHLA-DR from baseline (pre-OP) to post-OP (visit 4) and day 3 (visit 5) post-OP.2.Area under the curve (AUC) of quantitative mHLA-DR expression between baseline (pre-OP), ICU admission, and days 1 (visit 4) and 3 (visit 5) post-OP.3.Change in inflammatory markers including cytokines (including white blood count, C-reactive protein, interleukin 6 [IL-6], IL-10, multiplex enzyme-linked immunosorbent assay, inflammatory markers) and immune cell phenotype (flow cytometry) from pre-OP to days 1 (visit 4) and 3 (visit 5) post-OP.4.Change in organ dysfunction (Sequential Organ Failure Assessment scores including subscores) from baseline (pre-OP) to days 1 (visit 4) and 3 (visit 5) post-OP.5.Length of ICU/hospital stay (days after ICU admission) and total days in hospital.6.Cumulative Therapeutic Intervention Scoring System (TISS) points (resource need) while on ICU.7.ICU-, hospital-, 28-day, 60-day, and 90-day mortality.8.Total amount of infused fluids on ICU; including number and type of transfusions.9.Duration of vasoactive drug therapy, cum. vasopressor dose.10.Length of invasive mechanical ventilation (intubation to extubation), renal function (secondary) ECMO, or other circulatory supporting systems.

